## Abstract

**Introduction:**

Heightened rates of mental illness among children, young people and forcibly displaced adults are well-documented. Despite this, access to care in host countries is often low. Problem-management plus (PM+) is an intervention developed by the WHO that can be delivered through task-shifting by lay counsellors and has been shown to be effective in numerous studies. At the same time, it has been shown that PM+ has a limited effect on traumatic stress symptoms, a common problem among forcibly displaced individuals. In turn, to further these benefits, a novel emotional processing (EP) module has been developed to be adjunctively delivered alongside PM+(PM+EP).

**Method and analysis:**

The current study is a randomised controlled feasibility and acceptability study. 60 participants aged 16–25 will be randomly allocated to either PM+, PM+EP or care as usual. The primary outcome of this study will be the feasibility and acceptability of the delivery of PM+EP in forcibly displaced youth. Secondary outcomes are self-rated measures of distress, depression and anxiety, post-traumatic stress disorder, personally identified problems, hope, use of services and medications, general well-being and social support.

**Ethics and dissemination:**

Following ethical approval in February 2024, recruitment commenced in October 2024. Study completion is anticipated by December 2025. Findings will be disseminated via peer-reviewed publications, conference presentations and communication with relevant stakeholders.

**Trial registration number:**

NCT06878092.

STRENGTHS AND LIMITATIONS OF THIS STUDYThe trial includes three intervention arms, enabling comparison of accessibility and feasibility between problem management plus (PM+), PM+ Emotional Processing and care as usual in Sweden.The aim of the study is to understand the feasibility of implementing scalable psychological interventions in the Swedish context, with the primary aim to understand the safety and acceptability.The study will be implemented through collaboration between academics and civil society to facilitate future translation from research to practice.Both researchers and assessors will be blinded to intervention allocation, minimising risk of bias.

## Introduction

 According to the UNHCR, there are currently more than 120 million people globally who have been forcibly displaced from their homes.^1^ More than 35% of those displaced have been forced to leave their home countries and have resettled elsewhere as refugees or asylum seekers.^1^ The most recent humanitarian crisis, taking place in Ukraine, has resulted in an additional 15.5 million people being forcibly displaced from their homes with more than 7 million leaving Ukraine; this has resulted in Europe having to manage the largest influx of non-refugee migrants, refugees and asylum seekers since the second World War.^2^ Sweden has historically had an inclusive migration policy, but following policy changes in 2015,^3^ asylum applications have declined. In 2024, 9645 individuals applied, excluding Ukrainians covered by the Temporary Protection Directive, the most common countries of origin being Syria, Afghanistan and Iraq.^3^ Individuals who have sought protection in Sweden from Ukraine are entitled to protection in Sweden if they left Ukraine no earlier than 22 February 2022 according to the Temporary Protections Directive. This is a residence permit that is currently valid until spring 2026.^4^

Alarmingly, 40% of those who have been forcibly displaced are children under the age of 18, many of whom are unaccompanied minors.^1^ Experiencing displacement has been shown to be associated with developing poor mental health outcomes.^5^ The prevalence of common mental disorders in both child and adult forcibly displaced populations has been shown to be higher than for host populations. In a recent meta-analysis, the prevalence of post-traumatic stress disorder (PTSD), depression and anxiety disorders among refugee children was 22.71%, 13.81% and 15.77%, respectively.^5^ Another study investigating mental ill health in young refugees resettled in high-income countries (HICs) found substantially higher numbers of refugees experiencing ill health compared with their non-refugee peers.^6^

There exists a troubling discrepancy between the increased occurrence of mental health issues among forcibly displaced youth and their access to mental health services. Research in HICs has demonstrated that forcibly displaced children and adolescents access mental health services less frequently than their counterparts in the host country.^7 8^ Barriers to seeking mental healthcare may include language problems, lack of knowledge about the health system, cultural differences and stigma.^9^ In Sweden, young migrants are less likely to receive a wide range of psychiatric diagnoses but also less likely to receive adequate treatment.^10^ Additionally, there are examples of existing laws in Europe that limit the ability of refugees and asylum seekers to access healthcare. In Sweden, adult asylum seekers older than 18 years have healthcare access limited to ‘treatment that cannot be deferred’, which excludes their rights to receive regular health care.^11^ There are several evidence-based psychological interventions that have been adapted for refugee populations, such as narrative exposure therapy,^12^ common elements treatment approach^13^ and multimodal interventions, such as family-based mental health promotion.^14^

Scalable psychological interventions that can be delivered by non-professional helpers have been developed and used as one option to address the large mental health treatment gap.^15^ Scalable interventions often use task-sharing approaches characterised by the redelegation of tasks performed by highly specialised mental health staff to those with less or no formal training, such as community members.^16^ Additionally, scalable interventions are often brief, transdiagnostic and focus on developing skills for self-management instead of treating disorders. The helpers who implement these interventions among forcibly displaced populations are often from similar ethnic, cultural, or language backgrounds.

One of the earliest developed scalable psychological interventions was problem management plus (PM+),^17^ which aimed to allow for mental health services to be delivered in places with limited mental health resources. PM+specifically targets people experiencing moderate levels of psychological distress and aims to relieve symptoms related to common mental disorders. The intervention is composed of evidence-based strategies related to problem-solving and behavioural activation and consists of four core components: (1) managing stress, (2) managing problems, (3) get going, keep doing, and (4) strengthening social support.^17^ Several studies have demonstrated the effectiveness of PM+ in adults residing in low-income and middle-income countries through individual ^18 19^ and group formats.^20^,^22^ More recently, the feasibility and effectiveness of the intervention in HICs among refugees have been explored in the Netherlands^23^ and Switzerland.^24^ Although no active ingredients targeting post-traumatic stress symptoms are included in the intervention, PM+ has been shown to reduce individual symptoms of PTSD.^25^ The emotional processing (EP) Theory proposes that effective psychosocial interventions to treat PTSD should include direct modification of the fear structure, which may give rise to symptoms of the disorder, by activating the fear structure using exposure and by integrating more realistic, non-threatening information into it.^26^ Further, recent evidence indicates that processing positive memories and imagining positive events in the future can positively affect mental health outcome.^27^ Given the pervasiveness of experienced traumatic events and PTSD in refugee populations, including in children and adolescents,^5^ it would be worthwhile exploring further whether exposure to memories of negative past events adds to the efficacy of a scalable intervention such as PM+ in reducing symptoms of PTSD and depression, and additionally as to whether it would be feasible to deliver active ingredients of exposure therapy using scalable psychological interventions. To further elucidate the contribution of the retrieval of negative memories in reducing PTSD symptoms, this study seeks to preliminarily compare PM+ with PM+ including an EP component (PM+EP).^28^ The primary aim of this feasibility randomised controlled trial (RCT) study is to evaluate the feasibility and acceptability of the PM+EP and PM+ interventions for forcibly displaced youth residing in Sweden. A secondary aim of this work is to preliminarily compare PM+ with an EP component with PM+ and care of usual.

## Methodology

### Study setting

The study will be implemented through Save the Children Sweden. Save the Children Sweden has 58 000 members organised in 130 local associations. The local associations are united across 25 districts. Local associations and districts work in their local areas to build activities for children, develop networks and have channels for local decision-makers. They are also involved in Save the Children’s various campaigns, advocacy work and international humanitarian work. Since 2015, Save the Children has also developed a system of case managers across the country working with children who require different kinds of support, often when in contact with the Swedish welfare system. The study will be situated in three of the four regions (South, East and West).

### Trial design

The study consists of two phases: a feasibility RCT and a qualitative process evaluation. The feasibility RCT uses a three-armed single-blind randomised controlled parallel group design, comparing PM+, PM+EP and care as usual (CAU) for forcibly displaced persons living in Sweden. We aim to recruit 60 participants who screen positive for moderate psychological distress. Assessments will be conducted at baseline, 1 week after treatment completion (7 weeks) and 3 months after treatment completion (19 weeks). The flow chart of the trial is shown in figure 1. As part of the qualitative process evaluation, we will be exploring beneficiaries’ and implementers’ experiences with the intervention, and practitioners’ and policymakers’ thoughts on the use of PM+/PM+EP more widely in Sweden.

**Figure 1 F1:**
[figure not shown]
Study flow chart. CAU, care as usual; EP, emotional processing; PM, problem management.

The study started in June 2024 and data collection is estimated to finish by December 2025.

### Inclusion criteria

Participants will be eligible for the trial if they meet the following criteria:

Forcibly displaced youth aged 16–25 years old who arrived in Sweden after 2015.Elevated levels of psychological distress as determined through the Kessler-10 Psychological Distress Scale (K10; K10 >15).^29^Reduced levels of psychosocial functioning as measured by the WHO Disability Assessment Schedule (WHODAS 2.0>16).^30^Fluent in Swedish or in any language for which validated translations of the study manual and assessment tools were available.

### Exclusion criteria

Participants will be excluded from the study if they meet any of the following criteria:

An acute medical condition.Imminent suicide risk (assessed by the PM+manual suicidal thought interview).Indication of psychotic disorders and substance dependence (assessed by PM+manual observation checklist).Indication of severe cognitive or neurological impairment (assessed by PM+manual observation checklist).In the case of current psychotropic medication used: change in dosage during the past 2 months.

Approximately 20 individuals will be recruited for the qualitative process evaluation research, with five individuals recruited from each of the following categories:

Forcibly displaced youth (16–25 years old) who received either the PM+EP or PM+intervention; both completers and dropouts will be included where feasible.Family members or caregivers of trial participants.PM+ and PM+EP facilitators/helpers who conducted the intervention.Key informants, including but not limited to clinical supervisors of PM+/PM+EP facilitators, mental health specialists (eg,psychologists, psychiatrists), researchers and policy-makers.

### Informed consent

Potential participants in the study will be contacted by a member of the research team and will be provided with information about the study. Interested participants will be asked to provide informed consent prior to screening for potential participation in the trial. Participants will be asked to sign physical copies of the informed consent and to subsequently post the completed forms to Karolinska Institute (KI).

### Interventions

The trial will consist of three intervention arms: PM+, PM+EP and CAU.

### Problem management plus

PM+ is a brief, potentially scalable psychological intervention developed by the WHO and is delivered by non-specialised helpers.^17^ In brief, the intervention is based on cognitive behavioural therapy techniques and typically consists of 5 weekly, 90 min sessions. Participants are taught the following techniques during the sessions: stress management, problem-solving, behavioural activation and accessing social support (WHO, 2016). The intervention is described in detail elsewhere.^17^

For this study, a translated and adapted version (to the Swedish context) of PM+ will be used to match the exposure between the two active intervention arms. There will be 6 weekly 75 min sessions as opposed to 5. For the PM+arm, the additional session will include non-directive supportive counselling to match the time spent on the ‘emotional processing’ module.

### PM+ with EP module (PM+EP)

The PM+ strategies discussed above are identical across both interventions apart from the additional EP module.^28^ The additional module aims to provide a safe environment for participants to engage in the EP of both positive and negative memories. During the additional session, participants will be asked to imagine significant memories as pieces of a jigsaw puzzle; participants will be asked to elicit three memories, two positive/pleasurable and one negative/frightening. Participants will be assisted in processing these memories through discussing the puzzle pieces, the thoughts and emotions that come with the memory, and future perspectives. Participants will be asked to rate the intensity of emotions before and after they talk about their memories each time they are brought up.^28^ By constructing a life story, the participant is provided with the opportunity to adequately contextualise significant events, which may facilitate the recognition of interrelated emotional networks of experiences. Since this module will be added to a transdiagnostic intervention to reduce psychological distress, the distressing event may be a traumatic event, or any other adverse event (AE) with negative impact. Previous research has indicated that interventions involving exposure to traumatic memories can be safely administered to adolescents through the process of task-shifting.^31^ The additional module includes the following specific components:

Psychoeducation: Participants will be informed about the rationale behind the module and the mechanisms associated with it.Choosing three pieces of their ‘jigsaw puzzle’ (memories): Participants will be asked to choose three memories, two of them being pleasurable memories and one difficult (distressing/frightening/upsetting) memory. Participants will be asked to give a label to each of these memories (eg, ‘leaving the country’, ‘meeting with best friend’).EP of memories: After the ‘puzzle’ is ready, participants will be asked to talk about the memories on their lifelines. Participants will be asked to first discuss the positive memory and then the difficult memory. Talking about the same difficult memory will last for three sessions. Each time it is discussed, a discussion about a positive memory will follow.Positive imagination for the future: The final part of this module aims to help participants to engage in positive thinking by asking them to imagine their future in a positive way.

The additional EP components will occur between sessions 3 and 6.

### Therapist competence and adherence

Both the PM+ and PM+EP interventions will be delivered by helpers with at least a high school degree, matched with the participants according to their language and cultural backgrounds. The helpers will be native speakers of the language that the participant speaks and will also have sufficient speaking ability in Swedish or English. Where participants prefer, native Swedish speaking helpers will be available to implement the intervention.

Prior to the study, helpers will receive a 9-day training that focuses on the PM+ and PM+EP strategies, with additional training on common mental health problems, basic counselling skills and self-care strategies. Following the training, helpers will be required to complete one practice case. Throughout their implementation of the intervention, helpers will receive clinical supervision (either individual or group supervision) weekly by a PM+/PM+EP trainer. Helpers will report adherence through two methods. First, they will fill in a self-rated fidelity checklist after each session. Second, audio recordings will be made for approximately 10% of the sessions, where participants consent to recording. The recordings will be scored independently by two research assistants.

### Care as usual

The comparison group will receive CAU. CAU for forcibly displaced youth (under the age of 18) in Sweden corresponds to primary healthcare, education, social protection services and specialised psychological treatment where required. However, adults are only able to access care that cannot be deferred. Once the individual has received their residence permit, they are able to access all the healthcare services offered. Save the Children has a large presence in providing social support and treatment for refugees nationally. This involves both psychosocial programming and having mental health clinics. For this study, participants will be recruited from ongoing psychosocial programming.

### Assessments

Table 1 presents all assessments and respective time points for administration. Screenings are conducted on paper and mailed to KI to be scored for inclusion. All other assessments will be administered remotely, with data entered directly through REDCap that will allow for the coding of instruments in multiple languages for ease of data collection and subsequent data analysis.

**Table 1 T1:** Standard Protocol Items: Recommendations for Interventional Trials: schedule of enrolment, interventions and assessments for the PM+EP/PM+trial

	Measures	Enrolment (-T1)	Screening (T0)	Baseline (T1)	Intervention	Postassessment (T2; 7 weeks)	3-month follow-up (T3; 19 weeks)
Enrolment							
Informed Consent		X					
Eligibility screen			X				
Allocation				X			
Interventions							
PM+EP							
PM+							
CAU							
Assessments							
Psychological distress	K10		X				
Impaired functioning	WHODAS 2.0		X				
Suicidal ideation	Suicide screener		X				
Depression symptoms	HSCL-25			X		X	X
Anxiety symptoms	HSCL-25			X		X	X
PTSD symptoms	PCL-5			X		X	X
Subjective well-being	WHO-5			X		X	X
Perceived problems	PSYCHLOPS			X		X	X
Agency	SHS-A			X		X	X
Social support	Bonding Social Capital			X		X	X
Post-migration stressors	PMLD			X		X	X
Traumatic experiences	TEC			X			X
Mental healthcare use	CSRI			X		X	X
Treatment fidelity	CSRI				X		

WHO PM+suicide screener (three items).

CSRI, Client Service Receipt Inventory; EP, emotional processing; HSCL-25, Hopkins Symptom Checklist (25-item); K10, Kessler psychological distress scale (10-item); PCL-5, PTSD Checklist for DSM-5; PM+, Problem Management Plus; PMLD, Post-Migration Living Difficulties; PSYCHLOPS, Psychological Outcomes Profiles; SHS-A, State Hope Scale (Agency Subscale); TEC, Traumatic Events Checklist; WHO-5, WHO-Five Well-Being Index; WHODAS 2.0, WHO Disability Assessment Schedule 2.0.

### Screening measures

The WHODAS 2.0 sociodemographic and disability assessment questionnaires will be collected at screening. The sociodemographic questionnaire will be used to collect information on age, sex, asylum status, marital status, education and work status, and living conditions. The WHODAS 2.0 is a questionnaire developed to measure health and disability.^30^ The 12-item version, which has been more commonly administered as a screening tool, will be used to understand levels of impaired functioning. Scores are rated on a 1 (none) to 5 (extreme) scale (range: 12–60), with higher scores indicating worsened levels of functioning. A score of 17 or higher will be used to indicate moderately impaired functioning. Minor adaptations of the questions have been made for this study to better suit youth populations.

The K10^29^ will be used to screen for levels of psychological distress. Items are scored on a scale of 1 (none of the time) to 5 (all of the time), with higher scores indicating higher levels of psychological distress experienced in the preceding month (range 10–50).^32 33^ To align with other PM+studies of refugees residing in HIC, we will use a cut-off score of 16 to indicate moderate levels of psychological distress.^23 24^

Finally, the imminent risk of suicide will be assessed using the three-item WHO PM+suicide screener.^34^ The first question posed to participants is whether ‘in the past month have (they) had serious thoughts or a plan to end your life?’. If the participant says no to this question, the questionnaire will end, and participants will be invited to participate in the trial dependent on their WHODAS 2.0 and K10 scores. If the participant says yes, two additional questions will be asked: (1) ‘Have you taken actions to end your life?’” and (2) ‘Do you plan to end your life in the next 2 weeks’. If the participant does not answer yes to these two questions, they will be included in the study and this information will be flagged to their PM+facilitator when providing support.

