### Assessor competence

Data will be collected remotely through telephone assessments. The assessors undergo a 2-day training on questionnaire administration, basic interviewing skills, common mental health disorders, psychological first aid and ethics of research. In addition to this, assessors will have the opportunity to receive supervision on needs for referral from clinical staff and on the assessments by the trainer. Assessors will be available for all languages included in the study. All assessors should be fluent in either Swedish or English. They will be blinded to the allocation of the participants; during follow-up assessments and subsequent to the intervention period, assessors will instruct participants not to reveal the intervention that they received. The assessors will be recruited by Save the Children Sweden.

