### Study procedure

Potential participants will be recruited through ongoing Save the Children Sweden activities in three regions of Sweden (East, South and West). Save the Children Sweden has available programmes for children, young people and caregivers nationally. In 2024, activities reached almost 40 000 children and young people. These programmes included psychosocial activities, group-based mental health support and safe meeting places where displaced persons were able to receive support. Recruiting staff at Save the Children will inform all young people about who may meet the eligibility criteria about the possibility of participating during their regular activities. If recruitment for the final sample size is not possible through ongoing Save the Children services, advertisements will be placed on social media with information about the study. Potential participants who indicate interest in participation are then referred to the study team and perform an initial screening assessment of eligibility using the WHODAS 2.0, K10 and a structured suicide risk evaluation assessment. Participants will be invited to the baseline assessment if they meet the eligibility criteria stated above and consent to participating in the trial. At baseline, participants will complete the following assessments: HSCL-25, PCL-5, PSYCHLOPS, WHO-5, bonding social capital, SHS-A and CSRI. In addition, participants will be asked to complete PMLD and the traumatic event checklists. Following the assessment, participants will be randomly assigned in a consecutive manner, using a 1:1:1 ratio for the randomisation process. The randomisation sequence will be computed by an independent researcher from KI using computerised software and allocation will be conducted by Save the Children Sweden; allocation is concealed from all study staff. Following the completion of the intervention, participants will be invited to complete 1-week postintervention (7-week) and 3-month follow-up (18-week) assessments.

After the 3-month follow-up, participants will be invited to take part in the qualitative process evaluation. Individual semistructured qualitative interviews will be conducted by researchers and psychologists. Interviews with participants and their families will be held in their preferred language. For key informants, interviews will be conducted on an ongoing basis throughout the trial, and for PM+EP/PM+helpers, at the conclusion of their final sessions.

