On the completion of the trial, participants identified as requiring more support will receive information and assistance in locating suitable and appropriate follow-up care. For those who were randomised into CAU, PM+ will be offered after the 3 months post-assessment.

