### Sample size

Since this is a pilot feasibility trial, no formal power calculations have been carried out. A total number of 60 forcibly displaced youth (20 in each arm) will be included in the study, allowing us to evaluate the feasibility and acceptability of the intervention in the proposed setting, as well as drop-out rates for a future definitive trial. This sample size was determined to be sufficient based on prior similar studies.^44 45^

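### The suicide-screen flag goes to the participant's PM+ facilitator, a role that the 20 of 60 participants in care as usual do not have until after the 3-month follow-up

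*Protocol article*

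**What the plan says.** Under Screening measures, the three-item WHO PM+ suicide screener opens with a question on serious thoughts of, or a plan for, ending one's life in the past month. "If the participant says yes, two additional questions will be asked", on actions already taken and on plans for the next two weeks. Participants who do not answer yes to those two, and who qualify on WHODAS 2.0 and K10, stay in: "they will be included in the study and this information will be flagged to their PM+facilitator when providing support". The sentence makes no exception for any arm.

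The rest of the article fixes who can have a facilitator, and when:

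- Table 1 puts the suicide screener at T0 only and allocation at T1. Study procedure confirms the order: "Following the assessment, participants will be randomly assigned in a consecutive manner, using a 1:1:1 ratio for the randomisation process".
- Therapist competence and adherence has helpers delivering PM+ and PM+EP. Care as usual describes existing services and has no helper.
- Study procedure: "For those who were randomised into CAU, PM+ will be offered after the 3 months post-assessment".
- Sample size: "A total number of 60 forcibly displaced youth (20 in each arm) will be included in the study".

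**The concern.** The rule is written for everyone who is enrolled after that pattern of answers, at a point when nobody's arm is known. Its one stated action needs a person who exists in only two of the three arms. A participant who discloses recent suicidal thoughts and is then allocated to PM+ or PM+EP is flagged to a helper who sees them in six weekly sessions under weekly clinical supervision. The same disclosure from someone allocated to CAU reaches no one under the rule as written.

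What is at stake is participant safety in a trial whose stated purpose includes safety. No estimate, error rate or feasibility threshold changes. The point also does not say that CAU participants are otherwise unattended. It concerns one safety action that is defined for all enrolled participants and can be carried out for two thirds of them.

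**Working it through.** **Inputs, all from the Protocol article**

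| Input | Value | Section |
|---|---|---|
| Total and per arm | 60; 20 per arm | Sample size |
| Allocation | 1:1:1, after baseline | Study procedure |
| Suicide screener | T0 only | Table 1 |
| Arms with a helper | PM+, PM+EP | Therapist competence and adherence |
| PM+ offered to CAU | after the 3-month assessment | Study procedure |
| 3-month assessment | week 19 (week 18 in Study procedure) | Trial design; Table 1 |

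**Step 1: size of the arm.** 60 × 1/(1+1+1) = 20, which reproduces the stated 20 per arm. CAU share: 20/60 = 33.3%.

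**Step 2: can a flagged person be in CAU?** Yes. The screen is completed before allocation, and a flagged participant is eligible for every arm.

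**Step 3: does the recipient exist in CAU?** No. Facilitators deliver PM+ and PM+EP only. CAU participants could first have one when PM+ is offered, after week 19 (or 18).

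**Step 4: does another stated provision carry the flag?**

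- *Exclusion criteria* remove imminent suicide risk. The flag concerns people who remain eligible after that.
- *Feasibility measures* provide for adverse events to be followed, with specialist referral as needed. That covers unwanted experiences during the study and does not route a screening answer.
- *Assessor competence*: "assessors will have the opportunity to receive supervision on needs for referral from clinical staff and on the assessments by the trainer". This is optional support, and assessors are not named as receiving the screening result. Screening is done on paper and mailed to the research institute for scoring (Assessments).
- *Care as usual* says that participants come from ongoing psychosocial programming. Nothing there passes the flag to that programme. The section adds that adults can use only care that cannot be deferred until they hold a residence permit.
- *Study procedure* offers help in finding care, but on completion of the trial.
- *Table 1* does not repeat the suicide screener at T2 or T3.

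None of these routes the flag.

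**Step 5: how likely is the gap to be met in practice?** The article gives no rate of ideation. If k of the 60 are flagged and 20 of the 60 are allocated to CAU at random, the probability that at least one flagged participant is in CAU is 1 − C(40,k)/C(60,k):

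- k = 1: 1 − 40/60 = 0.333
- k = 2: 1 − (40×39)/(60×59) = 0.559
- k = 3: 1 − (40×39×38)/(60×59×58) = 0.711
- k = 5: 1 − (40×39×38×37×36)/(60×59×58×57×56) = 0.880

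The values of k are assumptions, chosen to show the range.

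**The case against.** The best case against has four parts.

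1. **The text does not say that the facilitator is the only recipient.** That is correct; it is inferred because no other recipient is named. The article is also condensed, and an unseen safety procedure may cover CAU. This would carry weight if the article were silent on the matter. It is not: it states the trigger, the decision to include, the action and the recipient, and the recipient does not fit one arm. That is a rule fixed badly, which differs from a detail left to the full protocol.

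2. **The closing words of the sentence, about providing support, may limit it to the intervention arms.** This reading is possible. On it the sentence contradicts nothing, but CAU then has no stated action on the flag at all.

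3. **The stated clinical safeguards do not depend on arm, and what differs is one notification to a non-specialist helper.** The safeguards are real and they limit the seriousness of the point. They do not carry the screening answer, as Step 4 shows. The research team does hold the scored forms for all participants, which is why the remedy is easy, but the article assigns it nothing to do with this answer.

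4. **Twenty of 60 is the size of an arm, not a count of people affected.** This stands. Only CAU participants with the relevant pattern of answers are affected, and their number cannot be derived from the article.

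**Conclusion.** The concern holds. As written, the flag cannot be carried out for participants allocated to CAU (20 of 60, 33%) from allocation until after the 3-month assessment at week 19 (week 18 in one place). How a known suicidal-ideation answer is handled under this rule depends on random allocation.

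The conclusion rests on two things: reading the sentence as the whole of the stated rule, because no other recipient appears anywhere in the article, and the stated equal allocation. The probabilities of 33% to 88% also depend on assumed numbers of flagged participants. The point should be fixed because it concerns safety and the correction is small. It changes no statistical result.

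**What to change.** Amend the last sentence of the suicide-screener paragraph under Screening measures. For every enrolled participant whose answers trigger it, the flag goes at screening, before allocation, to a named clinically responsible role already in the trial, for example the clinical staff who supervise on referral needs (Assessor competence). In the PM+ and PM+EP arms it goes to the facilitator as well. What the clinical role then does is for the clinical lead to decide.

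The cost is one protocol sentence and a short procedure note, with no added participants, visits or measures. The downside is one small procedural step. A flag sent before allocation carries no information about the arm; any later action by the clinical role should not reach the blinded assessors in a form that reveals it. If enrolment has already finished, the sponsor can still check the CAU screening forms and carry the corrected rule into the future definitive trial.
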